## Methods/Design

### Design

Controlled trial with a random allocation of participants in two alternative branches:

1. Implementation of a multimodal psycho-educational program to improve quality of life in FM (intervention group).

2. Usual care of FM (control group).

Evaluation of treatment outcomes will be carried out at the patient level, with individual evaluation at baseline and 1, 2, 6, and 12 months after the beginning of the intervention.

### Setting and study sample

Three primary health care centres (Viladecans-2, Gavà-1 and Gavà-2) in the province of Barcelona (Catalonia, Spain) voluntarily participated for the study. The sample pool (n = 530) comprises only those patients included in a FM database of the Viladecans Hospital for the years 2005 and 2006. In the event of a lack of participants, the plan is to recruit patients with FM included in the database during the year 2007.

Patients considered for inclusion will be those aged 18–75 years-old, contactable by telephone, who meet the diagnostic criteria of FM established by the ACR. The following patients will be excluded: those with a diagnosis not based on the ACR criteria, those with cognitive impairment or suffering from physical, mental/psychiatric limitations or a severe concurrent rheumatologic illness that impedes participation in the study evaluations, those who are not expected to live at least 12 months and those without schooling.

To calculate the sample size it was taken into account that we need to obtain a difference of at least 5 points in the FIQ between those that respond and those who are resistant to the intervention. The criterion of 5 points is based on two previous studies conducted with Spanish fibromyalgia patients [21,22]. A total of 109 patients per condition is needed to conduct the study, assuming an alpha risk of 0.05 and a beta risk of < 0.20 in a bilateral contrast, a standard error of 12.1 reported in a previous study [21], and a 15% dropout rate.

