### Intervention program

Participants from the intervention group will undergo a multi-component psycho-educational program that deals with FM based on available scientific evidence. It includes measures and instruments that can be employed within the Catalan Primary Health Care, whereas the participants from the control group will receive only the treatment prescribed by their physician.

The intervention program consists of nine 2-hour sessions delivered during a two month period. Participants will be allocated in groups with a maximum of 18 subjects per group. All sessions will take place at the PC centres Gava-2 or Viladecans-2. The contents of each session are displayed in Table 2.

**Table 2 T2:** Summary of the intervention program.

**Session 1: **General information. Expectations of the patients. History of the illness. Principal and secondary symptoms in FM. Physiological mechanisms involved in the genesis of pain.
**Session 2: **Relaxation training-I
**Session 3: **Diagnosis. Pharmacological and non-pharmacological treatments. Prognosis. Current model of health care in Catalonia. Units specialized in the treatment of FM.
**Session 4: **Relaxation training-II
**Session 5: **Strategies to increase self-esteem and regulate emotions. Pain experience and recurrent invalidation. Social support (family and friends).
**Session 6: **Relaxation training-III
**Session 7: **Holistic medicine
**Session 8: **Relaxation training-IV
**Session 9: **Benefits of physical exercise in FM. Qualitative assessment of the intervention program. Resolving doubts. Discussion concerning the strengths and weaknesses of the intervention.

In order to avoid conversations concerning the psycho-educational program among patients from different groups, we will remind the participants from the intervention of the condition that they are not allowed to talk about the program with those persons that are not attending their group. Before baseline assessment, an explanatory note addressing this important issue will be delivered to the patients participating in the program.

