### Statistical analyses

Data collected will be analysed using SAS statistical analysis software (SAS Institute Inc. 1999. v8.0, 4th ed) and employing both quantitative and qualitative techniques.

First, the intervention and control groups will be compared in order to verify that there are no significant differences between them in socio-demographic terms, clinical baseline data, etc. We shall use mean and standard deviation (SD) in continuous variables and percentages in categorical variables. For comparisons we shall use the Student-T test for continuous variables and the Chi-square test for categorical variables. Non-parametric tests may also be used.

Given that we have one between-groups factor with two levels (2 Groups: Intervention and Control) and one within-subjects factor with five levels (Baseline and 4 follow-up assessments: 0, 1, 2, 6, and 12), a 2 × 5 mixed factorial ANOVA will be performed to study the effect of the psycho-educational program on the quality of life. Then, between-subjects planned comparisons may also be used (post-hoc comparisons with independent samples T-test). If we observe differences between groups in quality of life prior to treatment, one-way analyses of covariance will be carried out using baseline scores as a covariate). In addition, we shall carry out a logistic regression analysis taking the groups as dependent variable (the target variable is a categorical variable with two categories: Intervention and Control) and the collected measures as independent variables. This analysis will let us to know the association between the intervention and the cost of the healthcare resources, controlling for the rest of variables.

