**Figure 1 F1:**
[figure not shown]
Formulas for calculating the QALYs gained in the first and last six months after the beginning of the program.

In the Figure 1, d_0–6 _is the incremental treatment effect on change in EQ-5D utility score for the first 6 months and d_6–12_the incremental treatment effect on change in EQ-5D utility score for the last 6 months. These incremental treatment effects will be estimated using multivariate ordinary least squares regressions, adjusting for baseline differences among treatment groups. The covariates included in the models will be: age, gender, years of education, employment and marital status, baseline FIQ and EQ-5D utility scores, and type of medication prescribed. To address uncertainty in the ICUR sampling distribution, non-parametric bootstrapping with five thousand replications will be carried out for each treatment comparison [29].

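### The 109 per arm and the named FIQ analyses treat patients as independent, although one arm is treated in groups of up to 18; any positive within-group correlation takes power below 80% and inflates type I error

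*Protocol article*

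**What the plan says.** Under Design, the protocol article randomises individual participants to two arms and evaluates outcomes at the patient level.

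Under Setting and study sample it states "A total of 109 patients per condition is needed to conduct the study, assuming an alpha risk of 0.05". The other inputs are "a beta risk of < 0.20 in a bilateral contrast", a target difference ("we need to obtain a difference of at least 5 points in the FIQ") and "a standard error of 12.1 reported in a previous study [21], and a 15% dropout rate". No ICC, design effect or number of session groups appears among them.

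Under Intervention program, the active arm attends nine 2-hour sessions over two months: "Participants will be allocated in groups with a maximum of 18 subjects per group". Participants are asked not to discuss the program with people outside their own group. Controls receive only what their physician prescribes, so they are not grouped.

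Under Statistical analyses, "a 2 × 5 mixed factorial ANOVA will be performed to study the effect of the psycho-educational program on the quality of life". Its factors are arm and time. Independent-samples t-tests may follow, and baseline is used as a covariate only if the arms differ before treatment. Under Cost-utility analyses, costs are modelled by gamma regression and utility changes by ordinary least squares with a listed set of covariates; session group is not in that list. For the incremental cost-utility ratio (ICUR), "non-parametric bootstrapping with five thousand replications will be carried out for each treatment comparison".

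**The concern.** This is a partly nested design: individual randomisation, then grouped delivery in one arm only. Patients who attend the same sessions together can end up with more similar outcomes than patients in different groups. Session 5 covers emotions and social support, and session 9 includes discussion, so this is plausible here. The variance of the intervention-arm mean then has a between-group part that does not shrink as patients are added to a group.

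The sample size has no allowance for this, and the only correlation that the ANOVA handles is between repeated measures on one patient. Two things are at stake. The stated power would not be reached, and the standard error of the arm difference would be too small, so a nominal 5% test would reject more than 5% of the time under no effect. The same would apply to the standard errors of the utility regressions if these are fitted as listed.

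**Working it through.** **1. The article's own figure.** Inputs from Setting and study sample: two-sided alpha 0.05, power 80%, difference 5 FIQ points, 12.1, dropout 15%. The 12.1 is called a standard error but gives 109 only if used as an SD, and it is used so here.

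n per arm = 2 × (1.960 + 0.8416)² × 12.1² / 5² = 91.93, so 92. With dropout, 92 / 0.85 = 108.2, so 109. The stated figure reproduces exactly, with no clustering allowance. Power at 92 completers per arm is 80.03%, so there is no slack.

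**2. Number of groups.** 109 / 18 = 6.06, so at least 7 groups if none exceeds 18. Completers per arm: 109 × 0.85 = 92.65. Completers per group: m = 92.65 / 7 = 13.24.

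**3. Formulas.** The design effect applies to the intervention arm only:

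- DE = 1 + (m − 1) × ICC
- SE = 12.1 × √[(1 + DE) / 92.65]
- Power (normal) = Φ(5 / SE − 1.96)
- Type I error of the unadjusted test = 2 × [1 − Φ(1.96 × √(2 / (1 + DE)))]
- Satterthwaite df = (v₁ + v₀)² / [v₁² / 6 + v₀² / 91.65], where v₁ = 12.1² × DE / 92.65 and v₀ = 12.1² / 92.65; power then comes from the noncentral t distribution.

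Example at ICC 0.05: DE = 1 + 12.24 × 0.05 = 1.61; SE = 12.1 × √(2.61 / 92.65) = 2.03; 5 / 2.03 = 2.46; power = Φ(0.50) = 69%. With df of about 15.4, power is 64%.

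**4. Results.** The ICC is an assumption, shown as a range.

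| ICC | DE | Power, normal | Power, Satterthwaite | Type I error, unadjusted test |
|---|---|---|---|---|
| 0 | 1.00 | 80% | 77% | 5.0% |
| 0.01 | 1.12 | 78% | 74% | 5.7% |
| 0.02 | 1.24 | 76% | 71% | 6.4% |
| 0.05 | 1.61 | 69% | 64% | 8.6% |
| 0.10 | 2.22 | 60% | 53% | 12.3% |

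**5. Sensitivity to group size.** With 18 completers in every group and 92 per arm, normal-approximation power is 76.7%, 73.6%, 65.1% and 54.0% at ICC 0.01, 0.02, 0.05 and 0.10. The table is the milder scenario.

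**6. What baseline adjustment recovers.** Assume a correlation of 0.5 between baseline and follow-up FIQ, so that patient-level variance falls by 0.5² = 25%, and take ICC 0.05. Session-group variance arises after randomisation, so it is held at 0.05 × 12.1² = 7.32.

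- Control arm: 0.75 × 146.41 / 92.65 = 1.185
- Intervention arm: 7.32 / 7 + 0.75 × 0.95 × 146.41 / 92.65 = 1.046 + 1.126 = 2.172
- SE = √3.357 = 1.832; 5 / 1.832 = 2.73; power 78% (normal), 72% (Satterthwaite)

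A figure of 81% results only if baseline adjustment also shrinks the session-group variance by 25%.

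**The case against.** The strongest reply is that nothing in the article shows a positive ICC. At ICC 0 the 80% holds and the tests are valid; at 0.01 the damage is small (78% power, 5.7% type I error). That stands: the direction is certain for any positive ICC, but the size is not known. The number 18 is also a maximum, and smaller groups would weaken the effect.

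Several stronger readings are tempting and not supported:

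- A reader might infer that the groups are closed and that each has its own leaders. The article states only allocation to groups and the rule on talking outside them. It does not say who leads the sessions. If the same leaders ran every group, they would add no between-group variance.
- A reader might infer that every analysis, including the bootstrap and the gamma model, demonstrably ignores grouping. The resampling unit and the variance estimators are simply not stated, and a condensed article may leave them to a fuller document. The firm ground is the sample size, the ANOVA with its t-tests, and the explicit covariate list of the utility regressions.
- A reader might infer that baseline adjustment restores the target. It recovers only part of the loss, as step 6 of the working shows.

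It can also be said that baseline and repeated measurements add precision that the sample size ignores. This may offset lost power, but it does not correct a standard error that omits the group component. The article also makes baseline adjustment conditional on an observed imbalance.

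Lastly, keeping 218 patients discloses the shortfall and does not remove it. That is fair. Restoring 80% by sample size alone (normal approximation, 15.3 completers per group) would take 117, 125, 148 or 186 randomised per arm at ICC 0.01, 0.02, 0.05 or 0.10.

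**Conclusion.** Wrong as written. The 109 per arm is the independent-patients figure for a design in which one arm is clustered in about 7 groups, and the named FIQ analyses have no term for those groups. For any positive ICC the trial has less than the stated 80% power for 5 points, and the unadjusted tests exceed their nominal 5% level.

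Over an assumed ICC of 0.01 to 0.10, power is 78% to 60% by normal approximation (74% to 53% with Satterthwaite df), and the type I error is 5.7% to 12.3%. These figures rest on 7 equal groups, 15% dropout, equal total variance in both arms and an SD of 12.1. The documents do not support a single value within that range, nor a claim that power is certainly lost.

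**What to change.** Keep the 218 patients and change the following.

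1. **Sample size text** (Setting and study sample): restate power over an explicit ICC range starting at 0, with the assumed number and size of session groups.
2. **FIQ analysis** (Statistical analyses): record session group for each intervention patient. Replace the ANOVA and t-tests with a partly nested mixed model for the repeated FIQ scores, with a random session-group effect in the intervention arm only and Satterthwaite or Kenward-Roger df. Include baseline FIQ always, not only when an imbalance is seen.
3. **Cost-utility analyses**: allow for session group in the least-squares and gamma models and in the ICUR interval, with methods corrected for few clusters. Uncorrected cluster-robust standard errors are biased downward with about 7 groups. A simple whole-group bootstrap understates between-group variance by a factor of about (7 − 1) / 7 = 0.86, that is by about 14%.

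Cost: revised wording, one extra variable and a less favourable stated power; no extra patients. The small-sample df cost about 3.5 points of power even at ICC 0 (80.3% to 76.8%), which should be disclosed. Baseline adjustment offsets part of the loss: at ICC 0.05 and a baseline correlation of 0.5, expect about 78% by normal approximation and 72% with Satterthwaite df.

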### Data collection and ethical aspects

First, patients that meet the inclusion criteria will be phoned by a research assistant who is a psychologist. Second, the research assistant will make an appointment with those patients that agree to participate in the study. Third, written consent will be obtained before the beginning of the study. Participants will be provided with a general overview of the aims and activities of the study. They will be also informed that they may choose to drop out at any time with the guarantee that they will continue to receive the treatment considered most appropriate by their physician. Patients in the control group will receive the treatment considered most appropriate by their physician.

Results will be monitored and most of data collected by means of standard questionnaires conducted in face-to-face interview by the research assistant, who has been trained in the administration of the instruments. The research assistant does not know which study group the patients being interviewed belong to ("blind"). Follow-up assessments shall take place at 1, 2, 6 and 12 months after the inclusion of the patient (see Table 1).

**Table 1 T1:** Follow-up assessments.

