**Month 1**
• FIQ
• Sociodemographic variables: 1 question (current work situation)
• Pharmacological and non-pharmacological treatment received during the last month

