**Month 6**
• FIQ
• Sociodemographic variables: 1 question (current work situation)
• Pharmacological and non-pharmacological treatment received during the last four months
• CSRI-adapted version: use of healthcare and social services during the first six months (0–6 months)
• EuroQoL-5D

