**Month 12**
• FIQ
• Sociodemographic variables: 1 question (current work situation)
• Pharmacological and non-pharmacological treatment received during the last six months
• CSRI-adapted version: use of healthcare and social services during the first six months (6–12 months)
• EuroQoL-5D

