### Variables and instruments of measurement

The study protocol was approved by the research ethics committee of the Foundation Jordi Gol i Gorina (Barcelona) and consists of the following materials:

1. *Sociodemographic characteristics*: Gender, birth date, address, marital status, education level, work status.

2. *History of the illness*: age of onset, date of the first diagnosis, pharmacological treatments (oral antidepressants, benzodiazepines-hypnotics, muscular relaxants and non-steroid analgesic and anti-inflammatory medications) and non-pharmacological treatments (physical exercise, relaxation techniques, cognitive-behavioural therapy) received during the previous 6 months.

3. *Questionnaire on chronic medical condition*.

4. *Fibromyalgia Impact Questionnaire (FIQ-Spanish version) *[23]: Instrument that measures physical function, work, and well-being, and contains visual analogue scales (VAS) for pain, sleep, fatigue, stiffness, anxiety and depression. A total score may be obtained after normalization of some items (between 0–10) and adding them to the VAS. Total scores range between 0–80 (without job items), with a higher score indicating a negative impact.

5. *EuroQoL-5D questionnaire (EQ-5D – Spanish version) *[22]: Generic instrument of health-related quality of life. It has two parts: Part 1 records self-reported problems in each of five domains: mobility, self-care, usual activities, pain/discomfort and anxiety/depression. Each domain is divided into three levels of severity corresponding to no problems, some problems, and extreme problems. Part 2 records the subject's self-assessed health on a Visual Analogue Scale (VAS); it is a vertical 10 cm line on which the best and worst imaginable health states score 100 and 0, respectively.

6. *Client Service Receipt Inventory – adapted (CSRI – Spanish version) *[24]: questionnaire for collecting information about use of healthcare and social care services, other economic impacts (such as time off work due to illness) and socio-demographic information. The variant used in this study was designed to collect retrospective data on service utilisation during the first and last six months after the beginning of the treatment.

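### The interviewer is declared blind, yet the month 1 and 2 visits ask about non-drug treatment while the programme runs, and programme patients get a note about it before baseline

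*Protocol article*

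**What the plan says.** Under Data collection and ethical aspects, the protocol article describes "most of data collected by means of standard questionnaires conducted in face-to-face interview by the research assistant", and then says: "The research assistant does not know which study group the patients being interviewed belong to". No other data collector is described.

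Table 1 lists the content of each follow-up visit. The FIQ is taken at months 1, 2, 6 and 12, and the EQ-5D at months 6 and 12. A treatment item accompanies them every time:

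- months 1 and 2: "Pharmacological and non-pharmacological treatment received during the last month"
- month 6: "Pharmacological and non-pharmacological treatment received during the last four months"
- month 12: "Pharmacological and non-pharmacological treatment received during the last six months"

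The history item under Variables and instruments of measurement shows what the category covers: "non-pharmacological treatments (physical exercise, relaxation techniques, cognitive-behavioural therapy) received during the previous 6 months".

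The programme has nine sessions over two months (Intervention program). In Table 2, sessions 2, 4, 6 and 8 are relaxation training and session 9 covers exercise. Controls receive only what their physician prescribes.

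The Intervention program section also asks programme patients not to discuss the programme with people outside their group, and continues: "Before baseline assessment, an explanatory note addressing this important issue will be delivered to the patients participating in the program".

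**The concern.** Patients in this trial know whether they attend a group programme, so they cannot be blinded. The only blinding safeguard the article states is that the interviewer does not know the group. If that person also asks about the treatment that separates the arms, readers of the results would be told that assessment was blind when it may not have been.

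The outcomes at stake are the main ones. The FIQ is the basis of the sample size, and the EQ-5D utility score drives the QALYs. An interviewer who knows the arm can affect how items are explained, prompted and recorded. Any such effect would add to the bias already possible from unblinded patients.

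The note raises a second and distinct question. It concerns what patients know, not what the interviewer knows. A patient who has just learned of assignment to the programme may answer the baseline questionnaires differently from one who has not.

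**Working it through.** No arithmetic decides this point. The check is to set the statements side by side and compare the time windows.

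**1. Who asks.** The research assistant collects most of the data in person. Table 1 does not name who asks the treatment item, but no other route is described. The natural reading is that the declared-blind person asks it.

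**2. What is asked.** The list of exercise, relaxation and cognitive-behavioural therapy stands in the history item. Table 1 uses the same term without redefining it, so the same meaning is the natural one.

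**3. When it is asked.** The Design section times assessments from the beginning of the intervention. Taking the programme as months 0 to 2:

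| Visit | Look-back | Window (months) | Overlaps programme? |
|---|---|---|---|
| 1 | 1 month | 1 − 1 = 0 to 1 | yes |
| 2 | 1 month | 2 − 1 = 1 to 2 | yes |
| 6 | 4 months | 6 − 4 = 2 to 6 | no |
| 12 | 6 months | 12 − 6 = 6 to 12 | no |

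If the nine sessions are evenly spread (an assumption), four or five have been held by month 1, including the relaxation sessions 2 and 4. The exercise session is the ninth, so at month 1 the telling answer would concern relaxation.

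The service-use inventory at month 6 covers months 0 to 6, which includes the programme. It asks about healthcare and social services, so it is a weaker route to disclosure.

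**4. Sensitivity to the time origin.** Data collection and ethical aspects times visits from inclusion, not from the start of the intervention. Suppose inclusion comes L months before the programme starts. In programme time the windows become:

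- month 1: −L to 1 − L
- month 2: 1 − L to 2 − L
- month 6: 2 − L to 6 − L

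With L = 1, chosen only for illustration, these are −1 to 0, 0 to 1 and 1 to 5. Disclosure would then start at month 2, and the month 6 question would overlap the programme. The timing shifts, but the conflict remains.

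**5. Which assessments are exposed.** With timing from the start of the intervention, the arm can become known at month 1. Table 1 lists content and fixes no order, so the month 1 FIQ may come before or after the treatment question. The later assessments are exposed to carried-over knowledge whatever the order on the day, if the same person returns: 3 of 4 follow-up FIQs (months 2, 6, 12) and 2 of 2 follow-up EQ-5Ds (months 6, 12). This applies to patients whose answers disclosed the arm, not necessarily to all.

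**6. The baseline note.** The sentence before it addresses intervention participants, so its recipients are programme patients. As written, they know their arm before baseline. Baseline enters the analysis in three places:

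- as one of the five levels of the 2 × 5 mixed ANOVA;
- as the ANCOVA covariate, used only if the groups differ before treatment;
- as baseline FIQ and EQ-5D utility among the covariates of the QALY regressions.

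**7. Sample size.** The planned 109 per group does not depend on this point. It reproduces: 2 × (1.96 + 0.84)² × 12.1² / 5² rounds up to 92, and 92 / 0.85 rounds up to 109.

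**The case against.** **A yes need not identify the arm.** The protocol records exercise, relaxation and cognitive-behavioural therapy as treatment history for all patients, so it expects them outside the programme, and a control may report them at follow-up. This stands. A reader might infer that blinding fails for every patient from month 1. The documents support only that it cannot be relied on as described.

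**The later look-backs miss the programme.** This also stands under the Design section's timing. Exposure at months 6 and 12 then rests on the same interviewer having learned the arm at month 1 or 2, not on the treatment questions asked at those visits.

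**Order of questions is detail for the full protocol.** This is true, and the absence of an order is not the complaint. A reader might take the bullet order in Table 1 as the interview order and conclude that the EQ-5D always follows the treatment questions. The table does not say so. Asking the FIQ first would in any case protect only that day's score.

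**Programme patients are told not to talk about it.** Read literally, the instruction could cover the interviewer. Its stated purpose, however, is to prevent conversation between patients of different groups. Applied to the interviewer, it would stop patients from answering the treatment question truthfully.

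**The outcomes are self-reported.** The FIQ and EQ-5D rely partly on visual analogue scales and patients are unblinded anyway, so interviewer bias may be secondary. This limits the likely size but does not support the blinding claim.

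**Conclusion.** The point holds in a limited form. The statement that the interviewer is blind and the treatment questions at months 1 and 2 cannot both stand as written. Truthful answers are likely to disclose the arm in many cases, and later FIQ and EQ-5D interviews by the same person are then exposed. Separately, the note as described tells programme patients their arm before the baseline questionnaires.

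This rests on three natural but unstated readings: that the research assistant asks the treatment item, that the history item's examples apply to Table 1, and that the same person returns at later visits.

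The size of any bias cannot be estimated. A reader might set a supposed interviewer shift against the 5-point FIQ target, but the documents give no figure for such a shift and any percentage would be invented. Nor do they show that baseline scores were in fact distorted, or in which direction. The flaw is worth correcting because the remedy is cheap and the blinding claim would otherwise be repeated in the report.

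**What to change.** - At every visit, including baseline, have the FIQ and EQ-5D (where scheduled) completed before any question on treatment or service use, preferably by the patient on paper.
- Put the treatment-received and CSRI questions last.
- Deliver the explanatory note only after baseline is complete.
- Describe outcome assessment as blind only so far as these steps make it so. If the interviewer continues to administer the outcomes after hearing the treatment answers, at that visit or an earlier one, withdraw the claim.

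Reordering alone protects only the same day's scores. Self-completion also limits the effect of knowledge carried over from an earlier visit, which is why it is preferred.

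The cost is a change in the order of forms and in the timing of the note. No extra staff are needed and the sample size is unchanged. The small downside is some blank items on self-completed forms, limited by the exclusion of patients without schooling.
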